### Discontinuation of Study Intervention

Unexpected discontinuation of study intervention criteria is (1) deterioration of symptoms leading to MSC infusion intolerance; (2) occurrence of adverse events or abnormal laboratory test results leading to MSC infusion intolerance; (3) individual wishes of the subjects; (4) any reasonable situations that require the clinical trial to be halted; (5) researchers' decisions to halt the clinical trial.

Expulsion criteria are (1) non-compliance to the study protocol; (2) other reasons.

### Primary and Secondary Efficacy Endpoints

The primary study endpoint is defined as the first time of recurrence. The recurrence should meet all the following four requirements: occurrence of new symptoms or deterioration of original symptoms; symptoms lasting for more than 24 h; more than 30 days from the last recurrence; no other reasons to explain the recurrence.

Secondary endpoints include the times of recurrence, EDSS scores, MRI lesion numbers, OSIS (Opticospinal Impairment Scale) scores, Hauser walking index, and SF-36 (quality of life short Form-36) scores. MRI lesion numbers refer to the total numbers of the lesions on T2-weighted images of the brain, the cervical, and the thoracic spinal cord, respectively. The SF-36 questionnaire is one of the most widely used qualities of life measures and it has been translated and validated in China (28). It has eight multi-item domains including physical functioning, social function, role limitations related to physical problems, role limitations related to emotional problems, mental health, vitality, bodily pain, and general health perceptions. SF-36 results are presented in two categories of physical component summary (PCS) and mental component summary (MCS). EDSS scores, OSIS scores, Hauser walking index, and SF-36 scores will be assessed every 3 months.

Exploratory endpoints include: serum lymphocyte subsets (T helper cells, T suppressor cells, Natural Killer cells, and B lymphocytes), cytokines (Interleukin-2,4,6,10,17A, TNF-α, and IFN-γ), complements, serum anti-AQP4 antibody titers, average retinal nerve fiber layer (RNFL) thickness, etc.

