## Introduction

Neuromyelitis Optica spectrum disorder (NMOSD) is a severe disabling inflammatory autoimmune disease of the central nervous system (CNS) featured with recurrent relapses of optic neuritis and longitudinally extensive transverse myelitis (1). Autoantibodies against the water channel protein aquaporin-4 (AQP4) are the diagnostic markers of the disorder and more than two-thirds of patients meeting clinical criteria for NMOSD are AQP4-IgG seropositive (2, 3). Frequent relapses are associated with a stepwise accumulation of neurological disability. Therefore, relapse prevention is particularly important to reduce the risk of a systemic disability over time (4). Azathioprine and mycophenolate mofetil are the most commonly used therapies for patients with NMOSD (5, 6). Recently, some randomized clinical trials show that the use of B-cell depletion (rituximab, inebilizumab), interleukin-6 signaling blockade (tocilizumab, satralizumab), and complement inhibition (eculizumab) can reduce the risk of relapses in NMOSD (7–11). However, still, some patients who have had these therapies have relapsed. So far, the optimal first-line treatment to reduce relapse rate remains unclear. Furthermore, no drug has been proved to improve neurological disability in NMOSD patients.

Stem cells are a group of cells that are immortal and have unlimited renewal abilities. The types of stem cells usually used in the registered clinical trials include multipotent stem cells, hematopoietic stem cells, and mesenchymal stem cells. There are some pilot trials and cohort studies assessing the therapeutic effect of stem cell transplantation in NMOSD patients (12–14). Recently, autologous nonmyeloablative hematopoietic stem cell transplantation showed to be effective on prolonged drug-free remission with AQP4-IgG seroconversion to negative (12).

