## Methods and Analysis

### Setting and Participants

The study will be conducted in six clinical centers in Shanghai, China. The leading center is Shanghai Ren Ji Hospital, which is one of the main teaching hospitals of the Shanghai Jiao Tong University School of medicine. Ren Ji Hospital is also one of the biggest clinical centers of neuroimmunological disorders in China. The five branch centers are Shanghai Rui Jin Hospital, Shanghai Xin Hua Hospital, Shanghai General Hospital, Shanghai Sixth People's Hospital, and Shanghai Ninth People's Hospital. In this study protocol, only the patients who fulfilled the diagnostic criteria of NMOSD established by Wingerchuk et al. (26) will be included.

The study protocol has been approved by the Ethics Committees of Ren Ji Hospital (2016-071K).

Patients will be recruited from those neuro-immunological centers of Neurology departments in China. Eligible patients will be invited to participate. All the participants will receive adequate information about the nature, purpose, possible risk, and benefits of the trial, and about alternative therapeutic choices. A signed written informed consent form will be obtained from all the participants before enrollment.

The clinical study will be conducted in accordance with all the national regulations and complies with the principles of the World Medical Association Declaration of Helsinki—Ethical Principles for Medical Research Involving Human Subjects, with all its amendments, and also with the principles of Good Clinical Practice.

The clinical information collected including age, sex, past medical history, NMOSD attack time and frequency, corrected visual acuity by standard logarithmic visual acuity chart, Expanded Disability Status Scale (EDSS) score, Opticospinal Impairment Scale (OSIS) score, Hauser walking index, quality of life short Form-36 (SF-36) score, serum status of anti-AQP4 antibody (tested in a cell-based assay), laboratory tests as listed in Table 1, electrocardiogram, abdominal ultrasound, chest X-ray or computed tomography, optical coherence tomography, number of brain and spinal cord lesions on MR images, immunomodulatory drugs used in the past 6 months, etc.

**Table 1 T1:** Schedule of activities of human umbilical cord mesenchymal stem cells (hUC–MSCs) to treat neuromyelitis optica spectrum disorder (hUC–MSC–NMOSD) study.

**Follow-up Period**	**V0** **(Screening)**	**V1** **(Baseline)**	**V2**	**V3**	**V4**	**V5**	**V6**	**V7**	**V8**	**V9**

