Time	**−30 ~ −1d**	**0**	**3M ± 7d**	**6M ± 7d**	**9M ± 7d**	**12M ± 7d**	**15M ± 7d**	**18M ± 7d**	**21M ± 7d**	**24M ± 7d**
General characteristics	√									
Inclusion and exclusion criteria	√									
Informed consent	√									
Physical examination	√		√	√	√	√	√	√	√	√
EDSS score	√		√	√	√	√	√	√	√	√
OSIS score	√		√	√	√	√	√	√	√	√
Hauser walking index	√		√	√	√	√	√	√	√	√
SF-36 score	√		√	√	√	√	√	√	√	√
Exploratory endpoints associated tests	√		√	√	√	√	√	√	√	√
Complete blood counts	√		√	√	√	√	√	√	√	√
Urinalysis	√		√	√	√	√	√	√	√	√
Coagulation function	√		√	√	√	√	√	√	√	√
Liver and kidney function	√		√	√	√	√	√	√	√	√
Serum glucose	√		√	√	√	√	√	√	√	√
Serum electrolyte	√		√	√	√	√	√	√	√	√
Thyroid function	√									
Urine HCG	√		√	√	√	√	√	√	√	√
Tests for infective diseases	√				√					√
Tumor markers	√		√	√	√	√	√	√	√	√
EKG	√		√	√	√	√	√	√	√	√
Abdominal ultrasound.	√		√	√	√	√	√	√	√	√
Chest X-ray or CT	√		√	√	√	√	√	√	√	√
MRI (head)	√					√				√
MRI (spinal cord)	√					√				√
MRI (optical nerve)	√					√				√
OCT	√					√				√
Primary treatment	√	√	√	√	√	√	√	√	√	√
hUC-MSC or placebo treatment		√	√	√	√					
Record of AE		√	√	√	√	√	√	√	√	√
Record of combined medications	√		√	√	√	√	√	√	√	√

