### Follow-Up

Primary, secondary, exploratory endpoint events, and side effects will be evaluated in all participating subjects at baseline and every 3 months. Magnetic resonance scans and optical coherence tomography (OCT) will be evaluated at baseline, year 1, and year 2 of follow-up.

For safety consideration, during stage one of the trial, all the subjects will receive a telephone interview within 1 week after hUC–MSC infusion and then every 2 weeks until the second infusion. The telephone interview will include information on symptoms' change and side effects.

The study schedule is shown in Table 1.

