### Statistical Analysis

The Kolmogorov–Smirnov Z test will be used for checking data normality. Categorical variables will be summarized as counts (percentage) and continuous variables as the means (standard error, SE) or medians (interquartile ranges, IQR), if not normally distributed. For the primary endpoint of the first time of recurrence, survival analysis will be conducted to analyze between-group differences. The Kaplan–Meier estimates for time of recurrence are presented for all groups. Hazard ratios for the comparison of between groups and 95% CIs were calculated with the Cox proportional-hazards model. Prespecified subgroup analyses of the primary outcome were stratified by, EDSS score at baseline, disease duration, age at randomization, the total number of previous relapses, number of relapses 2 years before randomization, and regular treatment. For secondary outcomes, statistical comparisons between the groups will be performed using Student's *t*-test or the Mann–Whitney U test for continuous variables, as well as the chi-square and Fisher's exact tests for categorical variables, as deemed appropriate. Correlations between continuous variables will be assessed by Pearson's correlation coefficient or Spearman's correlation coefficient. All missing data were not imputed in this study.

In this study, two analysis sets will be required. For the safety set (SS) analysis, all safety indicators will be obtained from those who have undergone at least one dose of hUC–MSC infusions. For the effectiveness analysis set, the intention to treat (ITT) analysis set will be used.

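### The MRI secondary endpoint leaves out the optic nerve, which is scanned anyway, and a total T2 lesion count is an insensitive measure of new disease activity

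*Protocol article*

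**What the plan says.** The section Primary and Secondary Efficacy Endpoints makes the MRI measure one of six secondary endpoints: "Secondary endpoints include the times of recurrence, EDSS scores, MRI lesion numbers, OSIS (Opticospinal Impairment Scale) scores", followed by the Hauser walking index and SF-36. It then defines it: "MRI lesion numbers refer to the total numbers of the lesions on T2-weighted images of the brain, the cervical, and the thoracic spinal cord". The sentence in the article closes with the word respectively, which suggests one count per region, not a single sum.

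Four other places bear on the point:

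- **Introduction.** It characterises the disease by "recurrent relapses of optic neuritis and longitudinally extensive transverse myelitis".
- **Table 1 (Setting and Participants).** The row "MRI (optical nerve" is ticked at screening, month 12 and month 24, the same visits as the head and spinal cord MRI. Follow-Up gives the same timing: "Magnetic resonance scans and optical coherence tomography (OCT) will be evaluated at baseline, year 1, and year 2 of follow-up".
- **Baseline data (Setting and Participants).** The MRI variable collected is the "number of brain and spinal cord lesions on MR images", again without the optic nerve.
- **Statistical Analysis.** For secondary outcomes, "statistical comparisons between the groups will be performed using Student's *t*-test or the Mann–Whitney U test for continuous variables". The section does not say whether the MRI count is analysed as a value at the visit or as a change from screening.

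**The concern.** The article describes a disease of the optic nerve and of long cord lesions. Its one imaging secondary endpoint covers neither feature well. The optic nerve is outside the definition although it is imaged, so a new optic nerve lesion adds nothing to the endpoint. A count also ignores extent: a cord lesion that lengthens scores no change, and two that lengthen and join score one fewer. Finally, the total includes all lesions present before randomisation, on which treatment may have little effect.

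At stake is how informative a secondary endpoint is. It may show little difference between arms when new disease activity differs, and a fall in the count has more than one possible meaning.

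**Working it through.** The article states no mean, SD, effect or power for the MRI endpoint, so there is no figure to reproduce. The check compares the definition with the schedule and then looks at what a count can register.

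**1. Regions defined against regions scanned**

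| Region | Scanned at screening, month 12, month 24 (Table 1) | In the endpoint definition |
|---|---|---|
| Brain | yes | yes |
| Spinal cord | yes | yes (cervical and thoracic) |
| Optic nerve | yes | no |

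No other named endpoint uses the optic nerve MRI. The one structural measure of the optic pathway that is named, retinal nerve fibre layer thickness, is exploratory and comes from OCT.

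**2. What a total count registers**

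For one patient and one region, let T0 be the count at screening, N the new lesions, R the lesions that resolve, and M the reduction in the count through merging. At a later scan

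T = T0 + N − M − R.

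Lesions that lengthen without merging do not appear in the formula. M and R both lower the count, but M reflects extension and R reflects resolution. With an assumed T0 = 6 and N = R = 0, merging of 1, 2 or 3 pairs gives T = 5, 4 or 3. Lesion extent has grown in each case. How often this happens cannot be computed from the documents.

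**3. The weight of old lesions (assumed values, none from the documents)**

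Suppose 1.0 new lesion per patient on control and 0.6 on hUC–MSC, with no merging or resolution.

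- 6 old lesions: 6 + 1.0 = 7.0 against 6 + 0.6 = 6.6, a difference of 0.4/7.0 = 5.7%.
- 2 old lesions: 3.0 against 2.6, a difference of 0.4/3.0 = 13.3%.
- New lesions only: 1.0 against 0.6, a difference of 40%.

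The absolute difference is 0.4 in all three cases, so the percentages alone show no loss of information. Any loss comes through the variance. If counts are also assumed to be Poisson and the visit total is compared without baseline adjustment, the number of patients needed for equal power scales with the mean count:

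- 6 old lesions: [(7.0 + 6.6)/2] / [(1.0 + 0.6)/2] = 6.8/0.8 = 8.5 times as many patients as for a new-lesion count.
- 2 old lesions: 2.8/0.8 = 3.5 times.
- Change from screening analysed instead: T − T0 = N in this example, so the ratio is 1.

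The penalty thus runs from none to large, depending on the lesion burden and on an analysis choice that the article does not state. Change from screening removes old burden. It does not register extension and does not separate M from R.

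**The case against.** The case against has real weight, and most of it limits the point without removing it.

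- **Regional counts.** If each region is counted separately, a cord count is not mixed with brain lesions, and pooled illustrations overstate the old burden. This stands. It does not bring in the optic nerve or register extension.
- **Baseline handling and reading rules.** Change from screening, covariate adjustment and rules for confluent lesions are commonly left to a statistical analysis plan or imaging manual. This stands, and their absence from the article is no finding. But the regions and the counted quantity are fixed in the article.
- **Spurious benefit.** A reader might infer that merging could make hUC–MSC look better than it is. The documents do not support this. It would need more merging on hUC–MSC than on control. If the treatment limits extension, merging is more frequent on control, which lowers the control count and works against hUC–MSC. Stages 2 and 3 are randomised and described as double-blind.
- **Missed optic attacks.** A reader might also infer that optic neuritis goes unrecorded. It does not: an attack that meets the recurrence criteria counts in the primary endpoint and in the number of recurrences. OSIS is a secondary endpoint assessed every 3 months, visual acuity is collected, and retinal nerve fibre layer thickness is exploratory. The exploratory list is also open-ended, so an optic nerve MRI measure could sit there, although none is named.
- **Repair.** The Introduction gives tissue repair as part of the rationale. A count that can fall may show lesions resolving, whereas a count of new or enlarging lesions cannot. This is a good reason to keep the total count.

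**Conclusion.** The point holds in a limited form. The optic nerve is left out of the MRI endpoint although the article names optic neuritis as a characteristic feature and schedules the scan three times. This follows directly from the text. That a total count is insensitive to new activity, blind to extension, and ambiguous when lesions merge follows from the definition, whether it is read per region or as one sum.

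The size is unknown. The documents give no lesion counts, variances or merging frequencies, and the figures under the check are illustrations only. They do not show that old lesions swamp new activity in this trial. This is one of six secondary endpoints. It enters neither the sample size nor the analysis of time to first recurrence, so the primary conclusion is unaffected. It is best treated as a cheap improvement.

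**What to change.** In Primary and Secondary Efficacy Endpoints:

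1. Keep the total T2 lesion counts, and state that they are reported by region.
2. Add the optic nerve to the regions read.
3. Add a measure beside the total: the number of new or enlarging T2 lesions since the screening scan, at months 12 and 24, in the brain, cervical cord, thoracic cord and optic nerve.
4. State that scans are read blind to allocation. Blinding of investigators in stages 2 and 3 is already planned, so this only makes it explicit for the readers.

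The list of baseline MRI variables should then also include the optic nerve.

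The cost is protocol wording, slightly longer reading time because each scan is compared with the screening scan, and one more secondary measure to report. No extra scans are needed.

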### Adverse Events

Adverse events (AEs) refer to any unwanted symptoms or signs in a clinical investigation subject and do not necessarily have a causal relationship with the applied intervention (29). All AEs will be coded according to the WHO's Adverse Reactions Terminology. At the end of the clinical trial, the intensity and relationship of any AEs with the study intervention will be identified.

If any severe AE (SAE) is encountered, even with extremely low incidence, it will be reported to the trial's principal investigator, the stem cell research ethics committee, and the state supervision agency within 24 h of its occurrence.

There are two types of side effects that need intensive monitoring, side effects during infusion and long-term side effects.

Side effects during infusion include allergic reactions (such as fever, tachycardia, dyspnea) and systematic complications (infection, embolism, and multiple organ failure);

While monitoring long-term side effects, the following items will be tested every 3 months: tumor markers (AFP, CEA, CA199, CA125, CA153, and CA242); complete blood count and urinalysis, liver and kidney function, blood glucose and electrolyte, coagulation tests, tests for infective diseases (HIV, RPR, hepatitis B, and C; tested at baseline, 9 months and 2 years of follow-up), urine HCG; electrocardiogram, chest X-ray or CT, and abdominal ultrasound.

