The first stage of the trial, which will last 24 months, is an open-labeled study and will be carried out in the leading center only. The first stage aims to evaluate the safety of the infusion of hUC–MSC in NMOSD patients. Patients (*n* = 30) will be treated with three different doses of hUC–MSC. According to the process of enrollment, the first to the tenth participant is in the low-dose group (*n* = 10, 1 × 10^6^ MSC / kg·weight); the eleventh to the twentieth participant is in the medium-dose group (*n* = 10, 2 × 10^6^ MSC / kg·weight); the twenty-first to the thirtieth participant are in the high-dose group (*n* = 10, 5 × 10^6^ MSC / kg·weight). The study starts from the low dose. Only when the lower dose group ends the observation period of 3 months, the study will proceed to a higher dose group. In case of unacceptable toxic reaction occurs in the dose escalation, the study will be ended immediately. In relation to safety considerations, before enrolling the patients in the low-dose group, we will give a single medium dose of hUC–MSC to one patient and follow-up the therapy for one year. The outcome of this dosage will be used only for safety evaluation, not to evaluate the therapy's effectiveness.The second and third stages of the study protocol are part of the multi-center double-blinded randomized clinical trial. The second stage, which aims to screen out the optimal dosage, will last for 24 months and will be carried out in six centers (one leading center and five branch centers). Patients (*n* = 160) will be randomized into four groups: the low-, medium-, high-dose groups, and the controlled group (*n* = 40, respectively). In the second stage, we were seeking to determine the ‘optimal biological dose.’ The dose that allows reaching the optimal efficacy-toxicity trade-off is further selected and recommended to stage 3. The third stage, which aims to evaluate the effectiveness, will last for 24 months and will be developed in six centers. Patients (*n* = 320) will be randomized into two groups: the optimal dose group (*n* = 160) and the controlled group (*n* = 160). The third stage aims to evaluate the effectiveness and safety of hUC–MSC for NMOSD patients. The study flow chart is shown in Figure 1.

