Lan–DeMets alpha-spending function with an O'Brien–Fleming boundary will be used to control the family-wise of type I error. Inverse normal combination test will be used to combine data from stages 2 and 3 in the final analysis. An independent Data and Safety Monitoring Board (DSMB) will review and evaluate the accumulated study data for participant safety, study conduct, and progress at each stage of the study. Only members of DSMB could have access to the data and results of the analysis. The Ethics Committee will be notified of any amendment to the study protocol. DSMB can make recommendations to terminate the study based on one of the following conditions: a significant difference in terms of effectiveness between groups; a significant risk-benefit ratio in one group; low degree of success in a reasonable period (such as poor compliance, low incidence of endpoint events). The advice of the DSMB meeting will be shared with the steering committee of the trial.

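### Adverse-event intensity and relatedness are dated to the end of the trial, with no earlier time given, although several earlier safety decisions need them

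*Protocol article*

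**What the plan says.** The Adverse Events section fixes one time for grading and attribution: "At the end of the clinical trial, the intensity and relationship of any AEs with the study intervention will be identified". The paragraph after it sets a fast reporting duty: "If any severe AE (SAE) is encountered, even with extremely low incidence, it will be reported" to the principal investigator, the ethics committee and the state agency "within 24 h of its occurrence".

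Other sections set decisions during the trial that rest on toxicity:

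- Study Design, stage 1, escalation: "Only when the lower dose group ends the observation period of 3 months, the study will proceed to a higher dose group".
- Study Design, stage 1, stopping: "In case of unacceptable toxic reaction occurs in the dose escalation, the study will be ended immediately".
- Study Design, stage 2: "The dose that allows reaching the optimal efficacy-toxicity trade-off is further selected and recommended to stage 3".
- Discontinuation of Study Intervention: adverse events (AEs) that make the infusion intolerable are a ground for stopping it.
- Statistical Analysis: the DSMB "will review and evaluate the accumulated study data for participant safety, study conduct, and progress at each stage of the study", and one ground on which it may advise termination is "a significant risk-benefit ratio in one group".

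On data collection, Table 1 has AEs recorded at V1 to V9. The Follow-Up section has side effects evaluated at baseline and every 3 months, with telephone interviews in stage 1.

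**The concern.** A reaction cannot be called toxic and unacceptable without a judgement of how intense it is and whether the cells caused it. The same holds for weighing toxicity against efficacy when a dose is chosen, and for a DSMB judgement of risk against benefit. If sites follow the Adverse Events section as written, those judgements would be made on events that are recorded but neither graded nor attributed.

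Two things are at stake. A toxicity signal could be missed when the dose is raised or selected. And attribution made long after the event depends on recall; in open-label stage 1 it would also be made with the dose, and possibly the later course, known.

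This is not a detail left to a fuller document. The article states a time, and that time does not fit its other sections.

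**Working it through.** The plan gives no figure to reproduce. The check compares the stated time of assessment with the time of each decision that uses it.

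**Inputs**

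- Study period March 2019 to March 2025, which is 72 months (Study Design).
- Three consecutive stages of 24 months each (Study Design): 3 × 24 = 72 months, which matches the study period.
- Observation of 3 months per dose cohort before escalation (Study Design).
- One sentinel patient followed for one year before the low-dose cohort is enrolled (Study Design). The article does not say whether this year lies inside the study period.
- Each subject followed for 24 months (Study Design, Table 1).

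**Reading A: the end is the end of the whole trial, month 72**

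| Decision | Needs | Earliest month | Gap to month 72 |
|---|---|---|---|
| First escalation, sentinel year outside the period | intensity, causality | 3 | 72 − 3 = 69 months (5.75 years) |
| First escalation, sentinel year inside the period | intensity, causality | 12 + 3 = 15 | 72 − 15 = 57 months (4.75 years) |
| Second escalation | intensity, causality | 3 months later: 6 or 18 | 66 or 54 months (5.5 or 4.5 years) |
| Dose selection at the close of stage 2 | intensity, causality | 24 + 24 = 48 | 72 − 48 = 24 months |
| 24-hour report | intensity only | within a day of the event | up to the rest of the trial |

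The escalation gaps are upper bounds. They assume a whole cohort is enrolled at once, and every month of accrual shortens them by a month.

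**Reading B: the end is each subject's own 24-month visit**

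Escalation waits until the cohort's last subject has had 3 months of observation. That subject's assessment comes 24 − 3 = 21 months after the decision. For a subject enrolled k months earlier the gap is 21 − k months, so the cohort's assessment is complete only 21 months after the decision. On this reading, dose selection at the close of stage 2 need not come before the assessment. The escalation steps, the discontinuation criterion, any DSMB review during follow-up and the 24-hour report still do.

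**Does another passage supply an earlier time?** Table 1 and the Follow-Up section show that events are collected and side effects evaluated. Neither says that intensity or relatedness is assigned at those visits or calls.

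**The case against.** The strongest reply is that the sentence does not exclude earlier assessment. It follows the sentence on AE coding and may mean a final summary or adjudication. The rest of the article implies judgement in real time: a severe event cannot be reported within a day unless someone has called it severe, and intolerance of the infusion is itself an attribution. Subjects are observed in hospital for 2 to 4 days after each infusion and stage 1 subjects are telephoned. A condensed article may leave the grading scale and form fields to the full protocol.

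Much of this stands. A reader might infer that grading happens solely at the end; the text does not say so. But the implied real-time judgements are exactly what the stated time conflicts with, and no sentence reconciles the two.

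Three other stronger readings also fail:

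- **Late attribution would be unblinded in every stage.** The section on Group Allocation, Randomization, and Blinding keeps investigators blinded in stages 2 and 3 through the end of the study and data analysis. Stage 1 is open-label, so the dose would be known at any time; what delay adds there is recall and knowledge of the later course.
- **A serious event that is not severe goes unreported.** The article expands SAE as severe, but loose wording is a plausible explanation. The trigger is unclear; a gap in reporting is not shown.
- **The delay is five to six years throughout.** That is an upper bound for the first escalation and does not apply to dose selection.

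**Conclusion.** The point holds as a conflict between a stated time and the decisions that depend on it. The end of the trial is the one time given for judging intensity and relatedness, and it comes after both escalation steps, stage 1 stopping, infusion discontinuation and the 24-hour report on either reading. On the whole-trial reading it also comes after dose selection and after the DSMB reviews of the earlier stages.

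The size is about 2 years for dose selection on the whole-trial reading, up to 4.75 or 5.75 years for the first escalation, and about 21 months for escalation on the per-subject reading. These figures assume that the three 24-month stages run back to back as stated and that escalation occurs as early as the 3-month rule allows.

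The conclusion does not extend to AE collection, which is planned throughout. Nor does it make 24-hour reporting depend on causality, since the article sets no such condition.

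**What to change.** Amend the Adverse Events section so that:

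1. the investigator, blinded in stages 2 and 3, records intensity, seriousness and relatedness when each AE is reported;
2. these data are complete for the subjects concerned before each escalation, dose-selection and DSMB review;
3. only final coding and reconciliation are left to the end of the trial.

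If the present sentence was meant as a final adjudication, say so and state when the initial assessment is made. Reconcile it with Study Design, Discontinuation of Study Intervention and the DSMB paragraph of Statistical Analysis. Clarify the SAE wording as well, so that it is plain whether the 24-hour trigger is seriousness or intensity.

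The cost is a few case report form fields, the protocol wording and slightly more work at sites, since AEs are already recorded at every visit from V1. The Trial Quality Assurance section limits amendments to the case where an SAE has occurred, so the sponsor should check that this does not block a clarifying change.
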